### Measurement of transition

The primary outcome measure is the transition to psychosis, as defined by the CAARMS criteria [8] (see table 5).

**Table 5 T5:** Psychosis threshold due to CAARMS

	Intensity	Frequency
Unusual Thought Content	6	4-6

Non-bizarre Ideas	6	4-6

Perceptual Abnormalities	5-6	4-6

Disorganised Speech	6	4-6

After transition to psychosis, participants are assessed with the PANSS [40] and the PSYRATS [41], to rate the severity of symptoms. They are also assessed with the SCAN 2.1 [42] interview for diagnosis according to DSM-IV criteria.

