### Participants

All patients aged 14 to 35 years referred to the mental health services in The Hague, Rivierduinen (Leiden and surroundings) and the province of Friesland in the Netherlands will be pre-screened with the Prodromal Questionnaire [22] over a period of two years. Patients with a score above the cut-off point of 18 on the positive symptom subscale (45 items in total) will be assessed with the CAARMS [8]. Furthermore, all patients with a suspicion of a psychotic development referred by the mental health services in Amsterdam to the specialized early psychosis clinic of the department of Psychiatry at the Academic Medical Centre will be assessed with the CAARMS. Participants are eligible if the following criteria are met: a) age 14 to 35 years; b) a genetic risk or CAARMS-scores in the range of At Risk Mental State (See table 1, 2, 3); and c) an impairment in social functioning, (a SOFAS- score [23] of 50 or less and/or a drop in SOFAS score of 30%.). Patients are excluded if they meet any of the following criteria: a) current or previous usage of antipsychotic medication more than 15 mg Haloperidol equivalent; b) severe learning impairment; c) problems due to organic condition; d) insufficient competence in the Dutch language; e) history of psychosis.

**Table 1 T1:** group 2a Attenuated psychotic symptoms, Sub-threshold intensity

	Intensity	Frequency
Unusual Thought Content	3-5	3-6

Non-bizarre Ideas	3-5	3-6

Perceptual Abnormalities	3-4	3-6

Disorganised Speech	4-5	3-6

**Table 2 T2:** group 2b Attenuated psychotic symptoms, sub-threshold frequency

	Intensity	Frequency
Unusual Thought Content	6	3

Non-bizarre Ideas	6	3

Perceptual Abnormalities	5-6	3

Disorganised Speech	6	3

**Table 3 T3:** group 3, BLIPS Group

	Intensity	Frequency
Unusual Thought Content	6	4-6

Non-bizarre Ideas	6	4-6

Perceptual Abnormalities	5-6	4-6

Disorganised Speech	6	4-6

Symptoms occur less than one week and resolve spontaneously

Participation is voluntary. Informed consent is given in writing and with personal signatures. Persons under 16 years also require informed consent from a parent. Participants may withdraw their informed consent at any time, without any consequences for their treatment.

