### Instruments

The following instruments are used:

1. The Prodromal Questionnaire (authorized Dutch translation by [name], [name], [name]) [22] will be used to screen patients for psychosis-proneness in the general help-seeking population and is a 92-item self-reporting lifetime questionnaire, rated on a two point scale ('agree' and 'disagree'.) Of these items, 45 apply in the case of possible sub-clinical positive symptoms. When maximizing the true positive cases, Loewy et al. found a cut-off score of eight symptoms at the positive subscale predictive for an ARMS on the SIPS (a CAARMS look-alike) with a sensitivity of 90% and a specificity of 48% in a population that was referred because of suspected prodromal state [22]. Since we expect more false positives in the general help-seeking population, the cut-off score for the EDIE-screening is higher [26]. Patients are invited for a further structured clinical interview when the total score of positive symptoms exceeds 18.

2. The Comprehensive Assessment of At Risk Mental State (CAARMS [8], authorised Dutch version by [name], [name], [name], [name], [name]) [8] is a semi-structured interview that assesses sub-clinical psychotic symptoms in the last year before assessment. Both intensity and frequency of the symptoms are assessed, in order to dimensionally distinguish between not at risk, ARMS and psychosis (see table 1, 2, 3). The CAARMS has a good reliability. High scores on the CAARMS are predictive for transition into psychosis with a relative risk of 12.44 (95% CI = 1.5 - 103.41, *p *= 0.0025). An ARMS predicts psychosis onset within one year with good sensitivity (86%), specificity (91%), positive predictive value (80%) and negative predictive value (94%) [9,25].

3. Drug and alcohol use are assessed with the Composite International Diagnostic Interview (CIDI) [27]. The CIDI is a comprehensive, fully standardized instrument for assessing mental disorders according to the definitions and criteria of ICD-10 and DSM-IV. Good reliability and validity of the CIDI have been reported with all Kappa coefficients above .5 for reliability and above .7 for validity [28].

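### Table 5, which defines the primary endpoint, repeats the ranges of the eligible BLIPS group in Table 3 and omits the duration condition that separates the two

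*Protocol article*

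**What the plan says.** In the protocol article, Measurement of transition fixes the endpoint: "The primary outcome measure is the transition to psychosis, as defined by the CAARMS criteria [8] (see table 5". Table 5 is captioned "Psychosis threshold due to CAARMS" and lists an intensity and a frequency range for each of four CAARMS scales. No duration or non-resolution condition is printed with it.

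The Participants section admits patients with "a genetic risk or CAARMS-scores in the range of At Risk Mental State (See table 1, 2, 3". Table 3 is "group 3, BLIPS Group", and below its ranges stands the note "Symptoms occur less than one week and resolve spontaneously". The same section excludes patients with a "history of psychosis".

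The Instruments section explains how the CAARMS tells the states apart: "Both intensity and frequency of the symptoms are assessed, in order to dimensionally distinguish between not at risk, ARMS and psychosis (see table 1, 2," and the reference goes on to Table 3. Duration is not named there. That section also says that the interview covers the year before each assessment.

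**The concern.** An endpoint threshold has to separate the event from every state in which a patient may enter the trial. If the printed ranges for the endpoint and for one entry group coincide and the endpoint carries no further condition, three things follow from a literal reading.

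- A BLIPS entrant meets the psychosis threshold at or before entry.
- The same patient is eligible under Table 3 and could be excluded for a past psychosis.
- A new brief episode in follow-up that resolves by itself is an at-risk state by Table 3 and a primary event by Table 5.

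Both the chi-square comparison and the Kaplan-Meier curves depend on how such episodes are called. Events that are already present at entry cannot be prevented by treatment. Counting them would pull the comparison towards no effect.

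**Working it through.** No figure in the article depends on this point, so there is none to reproduce. The check is a comparison of the tables, followed by an illustration of size.

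**Step 1. Tables 3 and 5 side by side (intensity / frequency).**

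| Scale | Table 3, BLIPS (entry) | Table 5, psychosis (endpoint) |
|---|---|---|
| Unusual Thought Content | 6 / 4-6 | 6 / 4-6 |
| Non-bizarre Ideas | 6 / 4-6 | 6 / 4-6 |
| Perceptual Abnormalities | 5-6 / 4-6 | 5-6 / 4-6 |
| Disorganised Speech | 6 / 4-6 | 6 / 4-6 |
| Duration or resolution note | yes | none |

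Four scales with two entries each make 8 cells, and 8 of 8 agree. The note is the only printed difference.

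**Step 2. How far the overlap reaches.** Table 1 intensities (3-5, 3-5, 3-4, 4-5) all lie below those of Table 5. Table 2 frequency is 3 throughout, and Table 5 starts at 4. Neither group meets Table 5, so the overlap concerns BLIPS entrants only.

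**Step 3. Does another section supply the separator?** The Instruments section names intensity and frequency. On these two dimensions Tables 3 and 5 cannot be told apart, so its statement does not hold for this pair. No section gives a minimum duration for a transition or says outright that an episode before entry does not count. With a look-back of one year, an episode shortly before entry can still lie inside the window at the visits at months 2, 4, 6 and 9.

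**Step 4. Illustrative size.** Inputs from Power calculation: 35% transitions under usual treatment and a 50% reduction, so 35% × 0.5 = 17.5% with CBT. Assumption, not in the article: a share b of each arm is counted as an event through the overlap, and all other patients transition at the planned rates. Then

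- control rate = b + (1 − b) × 0.35
- CBT rate = b + (1 − b) × 0.175
- risk difference = (1 − b) × 0.175

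| b | Control | CBT | Difference | Relative risk |
|---|---|---|---|---|
| 0 | 0.350 | 0.175 | 0.175 | 0.50 |
| 2% | 0.363 | 0.1915 | 0.1715 | 0.53 |
| 5% | 0.3825 | 0.21625 | 0.16625 | 0.57 |
| 10% | 0.415 | 0.2575 | 0.1575 | 0.62 |
| 15% | 0.4475 | 0.29875 | 0.14875 | 0.67 |

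For b = 5%: 0.05 + 0.95 × 0.35 = 0.3825; 0.05 + 0.95 × 0.175 = 0.21625; 0.21625 / 0.3825 = 0.565.

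For b = 10%: 0.10 + 0.90 × 0.35 = 0.415; 0.10 + 0.90 × 0.175 = 0.2575; 0.2575 / 0.415 = 0.620.

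This is a worst case for each b, because every patient in that share is counted as an event in both arms.

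**The case against.** The strongest answer is that the article as a whole shows what was meant. The note under Table 3 implies that symptoms at this level are BLIPS if brief and self-resolving, and psychosis otherwise. Table 5 is also not the whole definition: the sentence before it points to the CAARMS criteria, which are cited but not shown and may contain the duration rule. The Design section counts participants who become psychotic during the eighteen months, and the survival analysis starts the clock at inclusion. Both argue against counting an episode that had resolved before entry. Admitting BLIPS patients while excluding a past psychosis is coherent only if a BLIPS is not a psychosis. Assessors are blinded, and their ratings are calibrated regularly.

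Most of this stands. A reader might infer that BLIPS entrants are in fact scored as transitions at baseline, or that the endpoint cannot separate entry state from event and the trial loses a known amount of power. The documents do not support that. They give no BLIPS share and do not show how raters apply the criteria. Nor do they show that new brief episodes would be equally common in both arms, since a therapy aimed at these symptoms might change their number.

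The objection does not remove the conflict in the text. The article prints the endpoint threshold and, in Instruments, the dimensions said to separate the states. Taken together, these do not separate BLIPS from psychosis. The separator has to be inferred from a note attached to a different table. For new brief episodes in follow-up, neither the word transition nor the time origin settles the classification.

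**Conclusion.** The point holds as a contradiction in the printed definition of the primary endpoint. Table 5 and Table 3 agree in all 8 cells, Table 5 lacks the condition that Table 3 carries, and the Instruments section names only the two dimensions on which they agree. This is a threshold stated wrongly in the article, and not just detail left to a fuller document.

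The effect on the result is unknown. Duration is probably the intended separator, and raters may have applied it from the CAARMS source. The shift in relative risk from 0.50 to about 0.57 or 0.62 rests on assumed shares of 5% and 10% and on a literal use of Table 5 in both arms. It is a worst-case illustration and not a forecast.

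**What to change.** Reconcile Table 3, Table 5 and the Instruments sentence on how the CAARMS distinguishes the states:

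- Under Table 5, state the duration or non-resolution condition of the CAARMS criteria that separates psychosis from BLIPS, and name that dimension in Instruments as well.
- State that a transition must have its onset after inclusion.
- State how a brief self-resolving episode during follow-up, including a recurrent BLIPS, is classified. The documents do not settle this, so the investigators should take it from the CAARMS criteria and write it down.
- Use the same rule at all major and minor visits.

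The cost is about one line under Table 5, with matching wording in Instruments and in what assessors are told. No new data are needed.

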### Fidelity checks

The inter-rater reliability of the CAARMS assessments will be fine-tuned every three months in a Group wise assessment and discussion of role-played cases. The reliability of each rater is assessed by monthly independent ratings of written reports of a CAARMS interview.

The inter-rater reliability of the assessment of the fidelity of therapists in delivering the manualised therapy is fine-tuned monthly in a Group wise assessment of audio taped sessions. The fidelity of each individual therapist is assessed by a sample of five audio-taped therapy sessions rated independently by five different assessors.

### Analyses

To determine baseline balance, several variables that are proven to be risk factors will be assessed, such as severity of ARMS-symptoms [43], heredity [44], growing up in a big city, stress and unhealthy behaviour of mother during pregnancy [45], migration and feelings of discrimination [35,36] and alcohol and drug use, including cannabis use [46]. If the baseline balance is disturbed, the analyses will be corrected for risk factors for transition to psychosis.

Missing data will be imputed by EM-algorithm. EM-algorithm recovers the complete factor loadings considerably better than simple imputation techniques [47,48].

Group differences will be analysed by unadjusted chi-square. Pearson's chi-square tests will be performed to analyse gender differences between the transition group and the non-transition group, Comparisons will be analysed on intention-to-treat, using the Statistical Package for the Social Sciences (SPSS for windows, version 17). Multiple logistic regression analyses will be used to explore which factors predict transition to psychosis within the UHR-group. To examine the effects of CBT on the positive symptoms reported on the first four scales of the CAARMS, analysis of co-variance will be used.

Survival analyses will be used to measure time to transition and risk factors for developing a first episode psychosis. We will conduct Kaplan-Meier curves to explore the cumulative probability of developing psychosis with inclusion in the study as entry point and last follow-up assessment after 18 months as the end point.

We will use the Mann-Whitney test to examine if people who made a transition scored significantly higher on the CAARMS and the SOFAS compared to patients who did not make a transition. We considered p-values less than 0.05 to be statistically significant.

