### Randomisation

Randomisation will be stratified by site, to rule out factors concerning the institutions, therapists and habitat. The random allocation lists are generated by a web-based automated randomization system. To guarantee a numeric balance across conditions the randomisation will be performed separately for each research site, in random permuted blocks of ten. The allocation list will be kept in a remote secure location and an independent person randomly allocates the included patients. Patients are randomised after providing informed consent. The randomisation status is confirmed by fax to the randomisation bureau by the different sites.

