### Power calculation

We calculated power on an expected transition rate of 35 percent over eighteen months with a 50 percent reduction of transitions in the CBT-group. The sample we need for a 2-tailed test of the proportions with an alpha of .05 and a power of .80 is 2 × 93 for the reduction of the transition to psychosis and 2 × 82 for the persistence of ARMS and 2 × 91 for the transition into psychosis. A conservative estimate of the drop-out rate is twenty percent per year in schizophrenia research [24]. With an estimated 30 percent drop-out over 18 months, we decided to include 240 persons in the trial. Interventions to minimize drop-outs are flexibility to location of therapy (the appointment can be at their home-address or some times by telephone or webcam), sending Christmas- and Birthday cards every year. For the participants that end up in the CBT-treatment group there is also the possibility for web-cam therapy. All the participants that complete the study will have a financial compensation for expenses made.

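### Covariate adjustment of the treatment comparison hangs on an undefined judgement of baseline balance, and the plan does not say which result leads once adjustment is triggered

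*Protocol article*

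**What the plan says.** All of the following is in the protocol article.

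- **Analyses, balance check:** "To determine baseline balance, several variables that are proven to be risk factors will be assessed, such as severity of ARMS-symptoms". The list continues with heredity, urban upbringing, maternal stress and behaviour in pregnancy, migration and discrimination, and alcohol and drug use. That makes six groups, given as examples rather than as a closed set.
- **Analyses, consequence:** "If the baseline balance is disturbed, the analyses will be corrected for risk factors for transition to psychosis". No threshold, model or covariate set follows, and no analysis is exempted.
- **Analyses, between-group test:** "Group differences will be analysed by unadjusted chi-square".
- **Randomisation:** "Randomisation will be stratified by site", in permuted blocks of ten, with a remotely held list and an independent person allocating. The Analyses section does not name site as an adjustment factor.
- **Power calculation:** "expected transition rate of 35 percent over eighteen months", "with a 50 percent reduction of transitions in the CBT-group", 240 randomised, 30 percent drop-out.

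**The concern.** With concealed, stratified randomisation, a baseline difference between arms is chance. How large it happens to be is a poor reason for choosing the analysis model. A baseline variable earns its place by predicting transition, and the plan already claims that for these variables. A strong predictor should be in the model even when it looks balanced.

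Three consequences follow from making adjustment conditional.

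1. The effect reported can change meaning. The unadjusted comparison is marginal. A corrected odds or hazard ratio is conditional on the covariates and generally lies further from 1.
2. Because the trigger is undefined and no result is named as leading, there is room to choose between two answers after both are known.
3. When the trigger does not fire, the precision available from prognostic covariates is given up.

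**Working it through.** **Plan's own figure.** There is none for the trigger. The nearest is 93 per arm for 80% power. At 35% versus 17.5%, the pooled two-sided formula gives 99 per arm, and 93 per arm gives power 0.779. The simulation below therefore uses both N = 186 (2 × 93) and N = 240.

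**1. How often would chance alone trigger correction?** Assumption, not in the text: balance counts as disturbed if any of k independent variables has p < 0.05. The formula is 1 − 0.95^k.

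- k = 6 (the listed groups): 1 − 0.95^6 = 0.265
- k = 7: 0.302
- k = 8: 0.337
- k = 10: 0.401

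At p < 0.10 (1 − 0.90^k) the values are 0.469 for k = 6 and 0.651 for k = 10. Positive correlation, plausible for migration with discrimination and for alcohol with drugs, would lower all of these.

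**2. What does the switch do to the result?** Simulation with 4,000 trials per scenario. Control 35% and CBT 17.5% come from the Power calculation section. The following are assumptions: seven independent standard-normal risk factors, log odds ratio 0.2 or 0.4 per SD each, trigger as in step 1, complete follow-up, no site effect. The trigger fired in about 30% of trials.

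*With a true effect (proportion significant):*

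| N | log-OR per SD | Unadjusted | Switch | Always adjusted | Adjusted and unadjusted disagree |
|---|---|---|---|---|---|
| 186 | 0.2 | 0.783 | 0.784 | 0.794 | 0.078 |
| 186 | 0.4 | 0.793 | 0.808 | 0.838 | 0.102 |
| 240 | 0.2 | 0.879 | 0.880 | 0.889 | 0.042 |
| 240 | 0.4 | 0.882 | 0.900 | 0.928 | 0.068 |

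*With no effect (35% in both arms):*

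| N | log-OR per SD | Unadjusted | Switch | Always adjusted | Better of the two |
|---|---|---|---|---|---|
| 186 | 0.2 | 0.053 | 0.052 | 0.058 | 0.070 |
| 186 | 0.4 | 0.052 | 0.049 | 0.057 | 0.078 |
| 240 | 0.2 | 0.050 | 0.048 | 0.053 | 0.066 |
| 240 | 0.4 | 0.045 | 0.043 | 0.046 | 0.066 |

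The simulation standard error at 0.05 is √(0.05 × 0.95 / 4000) = 0.0034.

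- Power gain of always adjusting over the switch: 0.010, 0.030, 0.009 and 0.028, so about 1 to 3 points. Over the unadjusted test: 0.011, 0.045, 0.010 and 0.046.
- At N = 186, always adjusting for seven covariates gave 0.057 to 0.058 under the null. This is slightly high, so part of the gain there may not be real. It is also a reason for a short list.
- The median odds ratio was 0.39 unadjusted, about 0.36 adjusted at log-OR 0.2 and 0.31 at 0.4. The direct check is (0.175/0.825)/(0.35/0.65) = 0.39. The shift reflects, at least in part, the move from a marginal to a conditional odds ratio, not bias.

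**3. How many covariates can the data carry?** Expected events with 120 per arm:

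- 35% versus 17.5%, no loss: 120 × 0.525 = 63
- 35% versus 17.5%, 30% contributing nothing: 84 × 0.525 = 44
- 25% control (lower end of the range in the Discussion) with the same halving: 120 × 0.375 = 45, or 84 × 0.375 = 32

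Taking the four recruiting regions in the Participants section as sites (3 terms), plus treatment and two single-term covariates, gives 6 coefficients. That is 44/6 = 7.3 to 63/6 = 10.5 events per coefficient, or 32/6 = 5.3 to 45/6 = 7.5 at the 25% rate.

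**The case against.** The strongest reply is that the section describes a sensible default with a fallback: an unadjusted chi-square, plus correction if randomisation happens to go badly. Much of this stands.

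- **Self-contradiction.** A reader might infer that an unadjusted chi-square contradicts a promise to correct the analyses. The text supports the default-and-fallback reading equally well, and it also names methods that can carry covariates (logistic regression, analysis of covariance, survival analysis). The fault is that no leading result is named.
- **Baseline significance tests.** A reader might infer these, but the text says only that balance will be assessed. The 0.05 criterion at the end of the section is not tied to balance. The trigger frequencies above are therefore illustrative.
- **Covariates picked because they look unbalanced.** The text does not say this. Correction is for risk factors, so selection is on prognostic grounds. Only the on/off decision depends on observed balance, and the list is open.
- **Type I error.** A reader might infer that the switch inflates it. A mechanical switch did not. The 0.066 to 0.078 requires choosing the better result after seeing both, which the plan does not propose but also does not exclude.
- **Power.** The gain is small and rests on assumed prognostic strength. With only one or two covariates of the same strength it would be smaller than the figures shown for seven.
- **Detail for the statistical analysis plan.** That plan, which is not shown, could supply a threshold and a list. It would not remove the conditionality, which is fixed in the protocol text.

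**Conclusion.** The point holds as a recommended improvement, not as a threat to the trial's validity. The protocol makes adjustment of its main comparison depend on observed balance, leaves trigger and covariate list undefined, and does not say which result leads when the trigger fires. Nothing elsewhere in the article removes this.

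The size is modest. Two candidate results would disagree on significance in about 4 to 10% of trials with the planned effect, the effect measure may switch between marginal and conditional, and about 1 to 3 points of power are forgone relative to fixed adjustment. Chance would trigger correction in about 27 to 40% of trials for 6 to 10 factors, but only if the trigger were any p < 0.05 on independent factors. The simulation figures rest on seven independent predictors of assumed strength and complete follow-up. The case against the rule itself does not need them: it rests on randomisation making imbalance a matter of chance, and on the plan's own description of the variables as proven risk factors.

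**What to change.** Delete the conditional sentence and name one primary model for transition by 18 months, fitted whatever the observed balance. For example: logistic regression on treatment, site (the stratification factor) and one or two prognostic variables already collected at baseline, such as a stated CAARMS severity score and family history. Keep the list that short, because events may number only 44 to 63, and fewer at a 25% control rate. Report the unadjusted chi-square as supportive and show baseline balance descriptively, without using it to choose the model.

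A pre-declared unadjusted primary analysis with adjusted sensitivity analyses would also remove the switch, but would forgo the precision.

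Cost: a sentence or two in the Analyses section, with no new data, visits or participants. The downsides are small: the primary odds ratio becomes a conditional estimate, and the model is slightly more complex than a chi-square.

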A possible strength is the two-stage screening procedure used to detect subjects at risk. Screening the entire help-seeking population referred to community mental health services with a two-stage strategy, can potentially detect more ARMS patients by uncovering at risk cases that would normally never be referred. Many pre-psychotic symptoms are not recognised during the regular referral process. Because we do not want to miss any patients, we probably will not only detect late prodromal patients, but also early prodromal patients. Therefore, this two-stage screening method will detect more ARMS patients than the existing referrals to the specialized clinic, but probably at the expense of more false positives. The referred patients are more likely to be late prodromal than the people recruited by screening. Screening with a highly specific screening tool eliminates most of those not at risk in the first stage. The selected percentage undergoes the second stage of screening with the CAARMS interview. In this enriched sample of (more) psychosis-prone individuals the assessment instruments will probably have a better predictive value. In concordance with previous research [50] we expect about 3.5% of the help-seeking population will have psychotic-like experiences and will have an at-risk mental state. In the selected group we expect the transition rate to be 25 to 35 percent over an 18 month period. If this two-stage screening process proves to be successful, this type of screening could be implemented in routine mental health care.

Another strength of our study is that it has a strong external and internal validity. Since this trial is implemented in a mental health setting, the results will immediately be relevant for clinical practice. All participants receive treatment in a regular outpatient treatment centre in the same way they would have received treatment if they were not enrolled in the study. The internal validity is fine-tuned by supervision of the therapists every two weeks. The researchers and research assistants have supervision every three months. The internal validity is measured by the inter-rater reliability of the CAARMS; the therapy is monitored regularly and reliable and valid instruments are used.

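### EM imputation followed by an ordinary chi-square or ANCOVA counts filled-in values as observed; depending on the unstated imputation model, this can raise type I error to about 8–17% or dilute the treatment effect

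*Protocol article*

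**What the plan says.** All of the analysis text is in the protocol article, Analyses section. On missing data it says: "Missing data will be imputed by EM-algorithm. EM-algorithm recovers the complete factor loadings considerably better than simple imputation techniques". No outcome is exempted. The text names no multiple imputation and no adjustment of standard errors.

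The same section continues: "Group differences will be analysed by unadjusted chi-square". It specifies intention-to-treat comparisons, analysis of covariance for the first four CAARMS scales, and significance at p below 0.05. It also plans survival analyses of time to transition, with Kaplan-Meier curves from inclusion to 18 months. The Abstract lists chi-square tests and survival analyses together as the methods for group differences.

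The endpoint is binary: "The primary outcome measure is the transition to psychosis, as defined by the CAARMS criteria". The Power calculation section assumes an "expected transition rate of 35 percent over eighteen months with a 50 percent reduction of transitions in the CBT-group" and ends: "With an estimated 30 percent drop-out over 18 months, we decided to include 240 persons in the trial".

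**The concern.** An EM fill puts one expected value into each gap. A standard chi-square or ANCOVA run on the completed file then uses the full sample size, as if every value had been measured. Two things suffer: the standard error, and possibly the estimate itself.

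The reason given for EM is recovery of factor loadings. Neither the transition comparison nor the ANCOVA estimates a factor loading, so that reason says nothing about the error rate of a two-arm comparison.

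The binary endpoint adds a further difficulty. Its expected value is a fraction, and a chi-square needs a rule for turning that fraction into yes or no. Each possible rule has different consequences, so the p-value for the primary outcome could depend on a software choice.

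**Working it through.** **Inputs.** 240 patients, taken as 120 per arm (Power calculation; balanced blocks under Randomisation). Missing share m = 0.30, from the planned drop-out. Rates 35% vs 17.5% (Power calculation); 35% in both arms under no effect. Two-sided 5%. Assumption: outcomes are missing completely at random. The plan's only error figure is the nominal 0.05; a test on observed cases alone reproduces it (5.0%), with power 74%. The 2 × 93 sample size is not used here.

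**1. Arm in the imputation model.** Let q = p(1 − p). The true variance of a filled arm mean is q/[n(1 − m)], because only n(1 − m) outcomes carry information.

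- (a) Expected value kept, complete-data variance q/n used: type I = 2[1 − Φ(1.96 × √(1 − m))]. At m = 0.30: 1.96 × 0.837 = 1.640, giving 10.1%.
- (b) One random yes/no draw adds variance mq/n: type I = 2[1 − Φ(1.96/√(1/(1 − m) + m))]. At m = 0.30: 1.96/√1.729 = 1.491, giving 13.6% (simulation 14.0%).
- (c) Fractions kept and compared by t-test, or ANCOVA on EM values without residual noise. The estimated variance also shrinks by (1 − m), so type I = 2[1 − Φ(1.96 × (1 − m))]. At m = 0.30: 1.96 × 0.70 = 1.372, giving 17.0% (simulation 17.4% and 17.5%). ANCOVA with residual noise added: 13.4%.

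The same formulas by missing share:

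| Missing | (a) | (b) | (c) |
|---|---|---|---|
| 10% | 6.3% | 7.5% | 7.8% |
| 20% | 8.0% | 10.4% | 11.7% |
| 30% | 10.1% | 13.6% | 17.0% |

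- (d) EM value from a model with arm and one baseline covariate, rounded to 0/1, then chi-square (simulation, 35% rate): 8.1% if the covariate is uninformative, 16.9% if its correlation is 0.5. At a 20% event rate with an uninformative covariate: 5.2%.

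**2. Arm left out.** Gaps in both arms are filled towards the pooled rate, so the expected difference is (1 − 0.30) × (−17.5) = −12.25 points.

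- One random draw: type I about 5%, power 58%.
- Expected value entered into the chi-square: type I about 2%, power 60%.
- Fractions compared by t-test: type I about 5%, power about 74%. The estimate is still diluted, and this is not the named test.
- ANCOVA: type I 4.6%.

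**3. Every gap rounded to no transition.** With equal random drop-out, type I is about 5% and power about 70%. With 40% vs 20% drop-out and a true rate of 35% in both arms, the apparent rates are 0.35 × 0.60 = 0.21 and 0.35 × 0.80 = 0.28. The standard error is √[(0.21 × 0.79 + 0.28 × 0.72)/120] = 0.0553, so z = 0.07/0.0553 = 1.265. The rejection rate is Φ(1.265 − 1.96), or about 24% (simulations of rounded fills: 24–26%). With 35% vs 25% drop-out, simulation gives 9–12%.

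**4. How much of the primary outcome is missing.** Transitions detected before drop-out are known. With constant hazards (an assumption), 35% transition and 30% drop-out give cumulative hazards −ln 0.65 = 0.431 and −ln 0.70 = 0.357. The share that drops out first is 0.357/0.788 × (1 − 0.65 × 0.70) = 0.247, or about 25%.

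**5. The remedy under the same conditions.** Multiple imputation by arm with Rubin's rules (20 imputations): type I 5.3% at a 35% rate and 5.4% at 20% (Monte Carlo error about 0.35 points), power 74.3%. A single random fill by arm shows 81.0% power; the excess comes from its inflated error rate.

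**The case against.** The strongest counter-argument is that a reader might infer that the primary test certainly fails to hold 5%. The documents do not support that. The article does not say whether arm enters the imputation model or how fractions become yes/no. Two plausible implementations hold about 5%: a random draw without arm, and rounding to no transition with equal drop-out. This stands, and it limits the claim to what can happen.

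It can also be said that the imputation sentence is generic, that factor loadings suggest questionnaire scales, and that an article leaves such detail to the full plan. This stands in part. Application to transition status is a reading, and that the fill is single is inferred from silence. But the sentence exempts nothing, and the method and its justification are stated, not omitted. The ANCOVA on CAARMS scales is exposed even on the narrow reading.

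Nor does 30% drop-out mean that only 168 of 240 primary outcomes would be seen. The Measurements section schedules CAARMS checks at months 2, 4, 6, 9, 12, 15 and 18, so earlier transitions are on record. The article also calls the drop-out basis conservative and lists retention measures. This stands and reduces the size, as the table shows.

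Finally, the planned survival analysis can censor drop-outs without imputation, so it need not be affected. This is correct, and the fix builds on it. The chi-square is nevertheless the first-named test for group differences.

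**Conclusion.** The concern holds in conditional form. As written, the rule pairs a fill-in method with tests that ignore the filling, and supports it with a reason unrelated to a treatment comparison. At about 30% missing, type I error can reach about 8–17% if arm is in the imputation model. At 20% missing the range is about 8–12%, and at 10% about 6–8%. If arm is left out, the level is kept or is conservative, but the effect is diluted to about 12 of 17.5 points and power of the chi-square falls to 58–60%, against 74% for observed cases. Rounding to no transition is safe for the level only with equal drop-out.

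These sizes assume a single fill that includes transition status, 120 per arm, and data missing completely at random except where unequal drop-out is stated. The documents do not show which implementation was intended, so a firm claim that the 5% level is lost would go too far.

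**What to change.** - **Primary outcome.** State that transition status is not imputed by EM. Make the time-to-transition analysis already planned the basis of the primary comparison, with drop-outs censored at their last CAARMS. This assumes that drop-out is unrelated to later risk given what is modelled, and the text should say so.
- **18-month proportion, where reported.** Use multiple imputation with arm, site, and baseline and earlier CAARMS in the model, combined by Rubin's rules.
- **Repeated scales.** Replace the single EM fill plus ANCOVA by multiple imputation or by a mixed model on all observed visits, with the baseline value as covariate.
- **Justification.** Remove the factor-loading argument, or confine it to any scale work where loadings are estimated.

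The cost is a change of wording and slightly more analysis work. No further patients or data are needed. Confidence intervals will be wider, because they then reflect the information actually collected.
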